### Anticipated outcomes

3.3

Prior neuroimaging research provides a strong theoretical basis for the expected neural changes in this study. A synthesis of 13 studies involving individuals aged over 60 years, including both cognitively healthy participants and those with MCI, demonstrates distinct functional activation patterns associated with cognitive reserve and compensatory mechanisms (Anthony and Lin, 2018). Specifically, medial temporal regions, such as the posterior cingulate cortex, parahippocampal gyrus, superior temporal gyrus, fusiform gyrus, medial temporal gyrus, superior temporal gyrus, and hippocampus, are consistently linked to cognitive reserve (Anthony and Lin, 2018). In contrast, frontal regions, including the medial, superior, and inferior frontal gyri, as well as the precentral gyrus, and the dorsal attention network are associated with compensatory processes (Anthony and Lin, 2018). Notably, a reduced signal ratio between temporal and frontal regions has been proposed as a marker of cognitive decline and neurodegeneration (Anthony and Lin, 2018).

Additional evidence from task-based fMRI studies indicates dynamic, stage-dependent neural changes. Increased activation of the left inferior prefrontal gyrus has been observed during memory encoding following cognitive training, whereas decreased activation in bilateral fronto-striatal regions has been reported during memory retrieval, suggesting improved neural efficiency (Belleville et al., 2023). Furthermore, education level appears to modulate neural activation patterns: individuals with lower educational attainment exhibit lower baseline activation in the right temporal lobe but demonstrate greater increases over time compared to those with higher education levels (Belleville et al., 2023). Complementary to fMRI, EEG has been established as a non-invasive and temporally sensitive biomarker for neurodegenerative processes. In Alzheimer’s disease, EEG findings typically include increased theta and delta power, decreased alpha and beta power (Baradaran et al., 2021), and disrupted functional connectivity across brain regions (Özbek et al., 2021). Similar findings involving 143 participants with 60 AD and 83 non-AD individuals have been shown in our previous study (Yu W. Y. et al., 2024).

Consistent with the hypothesis-generating nature of this pilot research, study outcomes are organized within a predefined inferential hierarchy. The primary outcome is designated as the principal efficacy endpoint and will serve as the main basis for evaluating intervention-related effects. The secondary outcome is pre-specified *a priori*; however, given the limited sample size typical of pilot studies, findings will be interpreted as supportive and hypothesis-generating rather than definitive. EEG, gut microbiota, and metabolomic measures are designated as exploratory outcomes. These measures are not powered for confirmatory inference and are intended primarily to generate preliminary effect-size estimates and identify candidate biomarkers for future adequately powered confirmatory trials.

Based on these findings, we anticipate that the primary outcome of this pilot trial is intervention-induced change in resting-state fMRI activation within the left medial temporal region, encompassing the hippocampus and parahippocampal gyrus, from baseline (T0) to post-intervention assessment at 6 months (T1). Increased resting-state fMRI activation in the left medial temporal region following recitation training is interpreted as reflecting enhanced cognitive reserve — the brain’s capacity to sustain normal cognitive function despite underlying neurodegenerative burden — consistent with the compensatory scaffolding framework of cognitive aging (Reuter-Lorenz and Park, 2014). We anticipate that the intervention group will demonstrate significantly greater increase in left medial temporal region activation compared to controls, with the effect expected to be more pronounced in participants with lower educational attainment — consistent with a compensatory neural response in individuals with lower a priori cognitive reserve (Stern et al., 2020).

The anticipated secondary outcome is intervention-induced change in task-based fMRI activation within bilateral fronto-striatal regions during active recitation of Chinese classics from T0 to T1. The fronto-striatal network — encompassing the dorsolateral prefrontal cortex, anterior cingulate cortex, caudate nucleus, and putamen — supports executive control, phonological working memory, and procedural learning, all of which are recruited during complex verbal recitation tasks (Ranjan and Singh, 2025). A training-induced decrease in fronto-striatal activation during recitation is the anticipated direction of effect, interpreted as increased neural efficiency: as recitation becomes more automatized through practice, the same cognitive output is achieved with lower metabolic demand, analogous to skill-learning-related neural efficiency observed in other trained cognitive domains (Kelly and Garavan, 2005).

EEG parameters and gut microbiota/metabolomic composition are designated as exploratory outcomes. Given that the study population comprises individuals with SCD, rather than overt neurodegenerative disease, significant alterations in EEG parameters may not be observed. EEG is included as an exploratory measure to characterize the electrophysiological signature of the SCD sample at baseline, and to detect any subclinical signal changes that may warrant inclusion as a sensitive biomarker in a future confirmatory trial. For the microbiota profile, the recitation training group is expected to show increased gut microbial alpha-diversity and enrichment of beneficial genera, including *Prevotella*, *Faecalibacterium*, and *Megamonas* (Sun Y. et al., 2023), as well as increased abundance of short-chain fatty acid-producing taxa, such as *Ruminococcus*, *Roseburia*, *Subdoligranulum*, and *Bifidobacterium* (Swarup et al., 2025), compared to controls. Results will be reported descriptively, including individual-level variability data, and effect sizes with 95% confidence intervals will be provided to inform the design of a future confirmatory trial.

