
Cognitive training programs often incorporate culturally tailored elements to enhance acceptability and engagement among participants. In practice, training materials delivered in English may be ineffective for individuals who do not understand the language. However, culturally matched cognitive training programs remain scarce in Chinese-speaking societies despite rapid demographic aging and the growing burden of dementia. Therefore, this study with Chinese cognitive training materials investigates whether this culture-match, structured cognitive training is related to outcomes in individuals with SCD and examines potential neurobiological and systemic correlates of any observed effects, such as blood inflammation marker (cortisol). Specifically, we propose to evaluate the impact of Chinese Classics recitation training through comprehensive multimodal assessments, including neuropsychological testing, functional magnetic resonance imaging (fMRI) (Rajah and D'Esposito, 2005; Anthony and Lin, 2018), electroencephalography (EEG) (Yu W. Y. et al., 2024), blood biomarker profiling (Teruya et al., 2021), and gut microbiota (Kuijer and Steenbergen, 2023) and fecal metabolomic analyses (Zhao et al., 2025). By integrating behavioral intervention with advanced neuroimaging and biomarker methodologies within a culturally grounded educational framework, this study seeks to address current gaps in the literature and provide population-specific evidence relevant to Chinese-speaking communities. Such an approach may contribute to the development of precision-oriented, low-risk intervention strategies for early cognitive decline in aging populations. We will primarily aim to evaluate the feasibility and acceptability of classical recitation training in older adults with subjective cognitive decline. As a secondary objective, we will investigate whether recitation training correlates with changes in neuroimaging markers associated with brain plasticity. Additionally, exploratory objectives include characterizing metabolomic and gut microbiota profiles and examining their potential associations with cognitive and neuroimaging outcomes. These exploratory analyses are designed to generate preliminary data and inform future hypothesis-driven research exploring potential pathways linking recitation training, gut-brain interactions, and neuroplasticity, representing a novel mechanistic framework.

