### Outcome measurement

2.5

As described in the Sample Size section, functional MRI serves as an exploratory mechanistic outcome measure, detecting changes in task-related brain activation. The unit of measurement will be the percentage change in whole-brain blood-oxygen-level-dependent signal (%). APOE genotyping will be offered as an optional ancillary component of the study and used for exploratory analyses to investigate potential associations between genetic risk and intervention outcomes.

All other outcomes are defined as secondary outcomes, including:

changes in resting-state EEG spectral activity;performance changes across 11 neuropsychological tests;APOE genotype distribution;circulating inflammatory and stress biomarkers (IL-6, TNF-*α*, high-sensitivity C-reactive protein, and cortisol);gut microbiota diversity (Shannon index);gut microbiota taxonomic composition; andfecal metabolomic profiles related to the gut–brain axis.

Detailed methodologies for each outcome measure are described in the following sections.

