##### Statistical analysis

2.5.2.5

Statistical analyses will be conducted within the framework of the general linear model (GLM). For the primary clinical outcomes (e.g., subjective cognitive measures, neuropsychological test scores), a linear mixed-effects model will be used to handle the repeated-measures structure of the data throughout baseline, post-intervention, and follow-ups, with time, group, and group × time interaction as fixed effects, and subject as a random effect. This approach naturally accommodates missing data under the missing-at-random (MAR) assumption without requiring complete cases. The primary analysis will follow the intention-to-treat principle, including all randomized participants regardless of adherence or dropout, with missing values handled using multiple imputation based on baseline characteristics and available follow-up data. A per-protocol sensitivity analysis will also be conducted, restricted to participants who complete at least 80% of the intervention sessions. Covariates to be included in adjusted models will comprise age, sex, years of education, and baseline cognitive scores, selected *a priori* for their known associations with cognitive outcomes in SCD populations.

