For the neuroimaging analyses, task-related regressors will be convolved with the canonical hemodynamic response function, and motion parameters will be included as nuisance covariates. A high-pass filter of 128 s will be applied to remove low-frequency drift. At the single-subject level, voxel-wise GLM analyses will be performed to identify task-related activation patterns. Contrasts of interest (e.g., recitation versus resting baseline) will be evaluated using directional T-contrasts. At the group level, individual contrast maps will be entered into second-level random-effects models. Directional two-sample T-tests will be used for between-group comparisons, and conditions with similar activation patterns may be combined to enhance statistical power. Statistical significance will be set at *p* < 0.05, corrected for multiple comparisons using the false discovery rate (FDR) at the voxel level. For exploratory analyses, an uncorrected threshold of *p* < 0.001 may be applied. Extracted effect sizes from predefined ROIs will be further analyzed using Statistical Product and Service Solutions (SPSS). One-way analysis of variance will be used to assess condition-related differences, while Spearman’s rank-order correlation will evaluate associations between neural activation and clinical variables (e.g., years of education and Cognitive Reserve Index questionnaire (CRI-q) scores). Statistical significance will be defined as *p* < 0.05.

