### Statistical methods

2.6

The primary efficacy analysis will be conducted using generalized linear mixed-effects models to analyze repeated measures data, with adjustment for relevant covariates. Microbiome analyses will be performed using DESeq2 to identify differentially abundant taxa and linear discriminant analysis effect size to detect potential microbial biomarkers. Metabolomic data will be analyzed using partial least squares discriminant analysis, and pathway enrichment analysis will be conducted using the MetaboAnalyst platform. Multi-omics integration will be performed using Spearman correlation-based network analysis and causal mediation analysis to investigate regulatory mechanisms along the gut-brain axis. Multiple comparisons will be corrected using FDR, with a threshold of *q* < 0.05. All statistical analyses will be conducted using R (version 4.4.0; R Core Team, 2024) and SPSS (version 29.0; IBM Corp., Armonk, NY, USA), with statistical significance set at *p* < 0.05.

Given the inherent complexity and multi-layered nature of multi-omics data, if the aforementioned methods are insufficient for comprehensive analysis, we will collaborate with the institutional Artificial Intelligence Center affiliated in our hospital to implement advanced analytical approaches. These may include machine learning, network-based modeling, and partial least squares regression, among others, to construct predictive models that characterize causal or associative relationships between biological markers and clinical outcomes (e.g., cognitive function and depression). The predictive performance of different models will be systematically compared.

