Collectively, the following theoretical models: cognitive reserve, neural compensation, and stress-axis modulation, provide the mechanistic foundation for the present trial. While multiple potential mechanisms may underlie the effects of classical recitation on cognitive function, our primary hypothesis is that classical recitation training will be associated with greater change in resting-state functional connectivity within the hippocampal-default mode network than controls, consistent with intervention-induced neuroplasticity in memory-relevant circuits. Our secondary hypothesis proposes that the stress-axis modulation pathway, whereby recitation-induced enhancement of vagal tone and attenuation of HPA axis reactivity diminish stress-related gut dysbiosis, consequently fostering the production of beneficial microbial metabolites and neuroplasticity. Exploratory hypotheses include associations between classical recitation and shifts in gut microbiota composition and in circulating metabolomic profiles. By integrating behavioral training with multimodal biological measurements, including neuroimaging and peripheral biomarker analyses, this study seeks to bridge cognitive neuroscience theory with measurable physiological outcomes in individuals with subjective cognitive decline.

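### The outcome hierarchy contradicts itself across sections, and the imaging model that is stated cannot estimate the outcome that section 3.3 calls primary

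*Protocol article*

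**What the plan says.** Section 3.3 (Anticipated outcomes) claims a predefined hierarchy. There, "the primary outcome of this pilot trial is intervention-induced change in resting-state fMRI activation within the left medial temporal region", from T0 to T1, and the primary outcome serves as the principal efficacy endpoint. Task-based fronto-striatal activation is the secondary outcome, and EEG, microbiota and metabolomics are exploratory.

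Elsewhere the article says:

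- Introduction: "We will primarily aim to evaluate the feasibility and acceptability of classical recitation training in older adults with subjective cognitive decline". Neuroimaging is a secondary objective.
- Section 2.5 (Outcome measurement): "functional MRI serves as an exploratory mechanistic outcome measure, detecting changes in task-related brain activation", and "The unit of measurement will be the percentage change in whole-brain blood-oxygen-level-dependent signal". Every other outcome is defined as secondary.
- Section 2.5.2.5 (Statistical analysis): "For the primary clinical outcomes (e.g., subjective cognitive measures, neuropsychological test scores), a linear mixed-effects model will be used". The last paragraph of section 2.3 counts cognitive test scores and subjective cognitive measures as secondary, and section 2.5 does the same for the neuropsychological tests.
- Section 3.1: "our primary hypothesis is that classical recitation training will be associated with greater change in resting-state functional connectivity within the hippocampal-default mode network".

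On analysis, section 2.5.2.5 says of the neuroimaging that "task-related regressors will be convolved with the canonical hemodynamic response function", with recitation against a resting baseline as the example contrast. Section 2.6 says: "The primary efficacy analysis will be conducted using generalized linear mixed-effects models to analyze repeated measures data". It does not name the outcome.

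**The concern.** A pilot may have a feasibility aim and a lead mechanistic endpoint side by side. It cannot rank the same measure differently in different sections and also claim a predefined hierarchy. Someone analysing the trial by section 2.5 would report resting-state imaging nowhere as primary. Someone using section 3.3 would report it as the efficacy result. Someone using section 2.5.2.5 could lead with cognitive scores. Each could cite the protocol.

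Two other rules depend on knowing which result is primary. Section 2.1 keeps analysts blinded until the primary analysis is complete. Section 3.2 contemplates ending recruitment early if statistically significant results appear. Neither says on which outcome.

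**Working it through.** **1. Ranks side by side.**

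| Measure | Introduction | 2.3 and 2.5 | 2.5.2.5 | 3.1 | 3.3 |
|---|---|---|---|---|---|
| Feasibility, acceptability | primary aim | not in the outcome list | – | – | not in the hierarchy |
| Resting fMRI, left medial temporal | imaging in general: secondary objective | not named | – | – | primary |
| Resting connectivity, hippocampus to default mode network | imaging in general: secondary objective | not named | – | primary hypothesis | – |
| Task fMRI | imaging in general: secondary objective | exploratory, whole-brain unit | model given, no rank | – | secondary, fronto-striatal |
| Cognitive scores | – | secondary | primary clinical | – | no rank given |
| EEG | – | secondary | – | – | exploratory |
| Microbiota, fecal metabolomics | exploratory | secondary | – | exploratory | exploratory |

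The labels are not all of one kind: the Introduction states an aim and section 3.1 a hypothesis, and section 2.5 gives fMRI the lead only by ranking everything else after it. Sections 2.5.2.5 and 3.3 both apply the word primary to outcomes, and they name different ones. That pair is already a contradiction.

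**2. Can the stated imaging model estimate the section 3.3 outcome?** The first-level model convolves task regressors with a haemodynamic response and tests contrasts such as recitation minus rest. A resting scan has no task onsets to convolve. In the contrast, rest is the reference, so it is subtracted and not estimated. The region-of-interest values described later in section 2.5.2.5 come after these task contrasts. The model therefore gives neither a resting-state regional measure nor the connectivity of section 3.1. Resting scans are acquired at baseline and six months (section 2.5.2.3), so the data exist; the stated model does not use them.

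**3. The plan's own figure.** Section 2.3 gives 383 per group for d = 0.18, one-tailed alpha 0.05 and power 0.80. The noncentral t calculation gives power 0.7997 at 382 and 0.8006 at 383 per group, so the figure is reproduced. It belongs to the neuropsychological scores. The target of 60 has no effect size or power attached, so the sample size section does not settle which imaging endpoint leads.

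**4. Size of the risk.** Suppose k candidates are each tested at 0.05 and the one to be called primary is chosen afterwards. The chance of at least one false positive is 1 − 0.95^k under independence, with a lower limit of 0.05 (full dependence) and an upper limit of 0.05k (Bonferroni bound).

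- k = 5: 1 − 0.95^5 = 0.226; range 5% to 25%.
- k = 4 (leaving out feasibility, which would normally be estimated and not tested): 1 − 0.95^4 = 0.185; range 5% to 20%.
- k = 2 (only the two statements that call an outcome primary): 1 − 0.95^2 = 0.0975; range 5% to 10%.

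Each k treats cognition as a single candidate.

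**The case against.** The best defence is that section 3.3, read alone, is quite specific. It fixes modality, side, region, time window, comparator and direction. The Introduction and section 3.1 speak of an aim and a hypothesis, not an outcome, and a condensed article may leave a resting-state pipeline to a fuller document. The study also calls itself hypothesis-generating, and section 2.6 applies a false discovery rate correction.

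Much of this stands, and it limits the point. A reader might infer that there are five rival primary outcomes and no fixed question at all; the mixed labels and the detail in section 3.3 do not support that. Absence of a resting-state pipeline would not by itself be a finding. But the conflicting ranks are in the article's own text, the false discovery rate correction does not decide which result is primary, and section 3.3 itself claims an efficacy endpoint.

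Other inferences also fail:

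- That the linear mixed model of section 2.5.2.5 conflicts with the generalized one of section 2.6. The first is a special case of the second. The gap is the unnamed outcome.
- That a whole-brain measure would blend a predicted increase with a predicted decrease. Section 3.3 predicts the increase in resting scans and the decrease in task scans.
- That three imaging quantities plus 11 neuropsychological tests make 14 primaries and a 51% error rate (1 − 0.95^14). Section 2.5.2.5 gives only examples, section 2.5.3 names six instruments, and scores from the same people are not independent.
- That feasibility is ignored. Adherence is defined and logged (sections 2.1 and 3.2), and dropout is monitored and its reasons recorded. What is missing is its place in the outcome list.

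**Conclusion.** The concern holds as an internal contradiction in the outcome hierarchy, together with a stated imaging model that does not fit the outcome called primary in section 3.3. It needs correcting before unblinding, because a hierarchy aligned after results are known protects nothing.

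The contradiction itself rests on no assumption. The error figures do: they assume testing each candidate at 0.05 and choosing after seeing results. On five candidates the chance is 5% to 25%, and 22.6% if independent. The documents do not show that such a choice is intended. The article reports a trial registration whose content is not shown, so whether the registry already fixes one primary outcome cannot be judged here. Nor do the documents say whether the regional measure or the connectivity measure is the better endpoint.

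**What to change.** Before unblinding, use one hierarchy in the Introduction and sections 2.3, 2.5, 2.5.2.5, 2.6, 3.1 and 3.3:

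- State feasibility as the primary aim and list its endpoints, for example retention, adherence, and completed T0 and T1 scans, as proportions with 95% confidence intervals.
- Name exactly one principal mechanistic endpoint: a defined resting-state measure, region and T0-to-T1 window. The authors must choose between the regional measure of section 3.3 and the connectivity measure of section 3.1.
- State one region-level between-group model that estimates it from the resting scans, and name that outcome in section 2.6.
- Drop the primary label for clinical scores in section 2.5.2.5, and make the unit in section 2.5 match the chosen endpoint.
- Give every other outcome the same rank in sections 2.5 and 3.3.

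The cost is wording and one added resting-state analysis. The resting scans and adherence logs are already planned, so no new data are needed.

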#### Gut microbiota profiling by full-length 16S rRNA gene sequencing

2.5.5

Full-length 16S rRNA gene sequencing will be performed using the PacBio Revio platform, enabling species-level taxonomic resolution for precise identification of microbial strains capable of producing neuroactive metabolites. PCR amplification will be conducted using universal primers 27F and 1492R, followed by SMRTbell library preparation and sequencing, yielding approximately 10,000 high-quality circular consensus sequencing (CCS) reads (Q30) per sample. Bioinformatic processing will be performed using QIIME2, with taxonomic classification based on the SILVA database. Downstream analyses will include alpha and beta diversity indices (e.g., Shannon index), taxonomic annotation, and differential abundance analysis between study groups using DESeq2. DNA extraction and library preparation procedures will follow those described by Tsai et al. (2025).

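### Seven genera are predicted to rise, but the stated taxon-level analyses are all-taxa screens not tied to that prediction; a small pre-specified family would serve it better (minor)

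*Protocol article*

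**What the plan says.** Section 3.3 (Anticipated outcomes) gives a direction for the microbiota: "the recitation training group is expected to show increased gut microbial alpha-diversity and enrichment of beneficial genera", with *Prevotella*, *Faecalibacterium* and *Megamonas* named. It adds "increased abundance of short-chain fatty acid-producing taxa", naming *Ruminococcus*, *Roseburia*, *Subdoligranulum* and *Bifidobacterium*. That makes seven genus names, all expected to rise relative to controls. Both lists are worded as examples, so neither is closed.

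Section 2.6 (Statistical methods) describes the analysis: "Microbiome analyses will be performed using DESeq2 to identify differentially abundant taxa and linear discriminant analysis effect size to detect potential microbial biomarkers". It adds: "Multiple comparisons will be corrected using FDR", at q < 0.05. Section 2.5.5 likewise plans "differential abundance analysis between study groups using DESeq2" and stresses species-level resolution. Neither section mentions the seven genera.

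On reporting, section 3.3 says "Results will be reported descriptively", with effect sizes and 95% confidence intervals. It does not say for which taxa. The same section calls the microbiota measures exploratory and not powered for confirmatory inference. It describes them as a source of preliminary effect sizes and candidate biomarkers for a later trial.

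**The concern.** A prediction about a handful of genera and a screen across every taxon are different questions. If the seven are tested only inside the screen, they share its multiplicity correction with all the taxa for which nothing was predicted. Some of the sensitivity available for the stated prediction is then lost without need.

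Two further matters follow. Because the lists are open, a genus that turns up in the screen could later be described as predicted. And unless it is settled which estimates will be shown, those carried to the next trial could be the ones that happened to pass q < 0.05, and such estimates are too large on average. The stakes are modest, since these are exploratory outcomes in a pilot. But effect sizes are what the pilot is meant to hand on, and a list of predictions is credible only if fixed before the data are seen.

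**Working it through.** **The plan's own power figure.** Section 2.3 gives one calculation, for neuropsychological scores: d = 0.18, one-tailed α = 0.05, power 0.80, 383 per group. The noncentral t gives 382.3, rounded up to 383, with power 0.8006, so it reproduces. No power figure is given for taxa.

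**Inputs from the article.**
- Named genera: 3 + 4 = 7.
- FDR threshold: q < 0.05.
- Completers: 36 per arm with 20% attrition gives 36 × 0.8 = 28.8, about 29. Section 2.3 expects at least 60 completers in total; using 30 per arm barely changes the results.

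**Inputs that are assumptions.** The number of taxa tested, m (50, 100 or 300); the true standardised difference, d; independent taxa; two-sided t-tests in place of DESeq2; all seven genera truly changed and no other taxon changed.

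**Why family size matters.** Benjamini–Hochberg rejects up to the largest k with p(k) ≤ 0.05·k/m. For a lone finding (k = 1) the bar is 0.05/7 = 0.0071 in a family of seven, but 0.05/50 = 0.001 or 0.05/100 = 0.0005 in a screen. With SE = √(2/29) = 0.263 and 56 degrees of freedom, a single test at d = 0.8 has power 60%, 35% and 28% at those three bars.

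**Simulation.** Draw 7 shifted and m − 7 null statistics, apply Benjamini–Hochberg at 0.05, and average the rejections over the seven. Several independent runs of thousands of replicates agree to within about two percentage points:

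| true d | family of 7 | m = 50 | m = 100 | m = 300 |
|---|---|---|---|---|
| 0.5 | 33% | 10% | 6% | 3% |
| 0.65 | 61% | 26% | 18–19% | 10% |
| 0.8 | 83% | 53% | 40–42% | 25–27% |
| 1.0 | 96% | 82–83% | 75% | 59–60% |

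**Sensitivity.**
- If only three of the seven truly change at d = 0.8, power is about 72% in the family of seven against 33–34% (m = 100) or 21–22% (m = 300).
- If 20 other taxa among 300 also change at d = 0.8, the screen rises to 44%, against 84% for the family.
- At d = 0.18, which the article gives for a different outcome, the figures are 2.5% for the family and 0.3% for m = 100. Neither analysis is useful there.

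**Selection on q.** With m = 100 or 300, predicted genera that pass the screen show a mean observed d of about 1.06–1.16, whether the true d is 0.5, 0.65 or 0.8. A smaller family does not cure this: at true d = 0.5, those passing the seven-genus family average about 0.80. If every genus is reported regardless of q, there is no such selection. The 95% CI half-width is then about 2.003 × 0.263 = 0.53 SD.

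**The case against.** The strongest reply is that the article already says what this trial can do. Section 3.3 calls the measures exploratory and not powered, and section 2.3 concedes that the sample is underpowered for the other multimodal outcomes. An all-taxa screen suits the stated aim of finding candidate biomarkers, and the genera appear in the Discussion as illustrations. How the FDR family is defined, and whether genera are aggregated, could sit in an analysis plan that is not shown. All of this stands, and it is why the point is minor. What remains is that the article does name the taxon-level methods and the threshold, and neither is linked to a prediction that it also makes.

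Three stronger readings are tempting and not supported.
- A reader might infer that most true changes in the predicted genera would be missed. That depends on m and d, which the article does not give. It fails at d = 1.0, where screen power is 59–82%, and at d = 0.8 with 50 taxa it is 53%.
- A reader might infer that the reported effects will be inflated. That happens only if estimates are selected by q-value. No passage limits reporting to taxa below 0.05, and section 3.3 promises effect sizes with confidence intervals. DESeq2 can supply an estimate and standard error for each taxon it tests.
- A reader might infer that the alpha-diversity prediction is also lost in the screen. It is not. The Shannon index is listed as its own outcome in section 2.5 and named separately in section 2.5.5.

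**Conclusion.** The point holds as a mismatch between a directional prediction for seven named genera and stated taxon-level analyses that are both untargeted. Treating the seven as their own family gave higher power in every setting examined. The gain is about 23 to 30 percentage points at d = 0.5 (33% against 3–10%), 30 to 58 at d = 0.8, and 14 to 37 at d = 1.0. At d = 0.5 the smaller family would still miss about two thirds of true changes, so it does not make the pilot well powered.

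These figures rest on an assumed taxon count, assumed effect sizes, independence between taxa, and t-tests in place of a count model. Sparse, overdispersed data could give different numbers. This is a minor, inexpensive improvement and not an error in the plan.

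**What to change.** In section 2.6, before any stool data are seen:

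1. Close the predicted list at the seven genera named in section 3.3.
2. Aggregate reads to genus level for these seven and analyse them as one FDR family at q < 0.05.
3. Report all seven estimates with 95% CIs whatever their q-values. This is the essential part, because it keeps the effect sizes passed to the next trial free of selection on significance.
4. Keep the Shannon index as its own outcome, outside this family, so that it carries no added multiplicity cost.
5. Keep the all-taxa DESeq2 and LEfSe screen as discovery with its own FDR family, and do not describe its other hits as predicted.

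The cost is a few lines of text and one small additional analysis of data already being collected. The downside is that a genus outside the closed list can only be a discovery finding.
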